### Sample Size Calculation

For our sample size calculations, we assumed a prevalence of undiagnosed cognitive impairment of 8%. Since little quantitative information is available on the prevalence of undiagnosed cognitive impairment, we based this assumption on four considerations. The first assumption is the prevalence of dementia in the Dutch population >65 years of age is around 16% [28].The prevalence of cognitive impairment will be even higher if MCI is also considered. The second is that around half of all patients with cognitive impairment are undiagnosed. The third is the prevalence of cognitive impairment is higher in people with diabetes. And the fourth is the oldest old, in whom dementia prevalence is highest, are least likely to participate in research projects.

In previous research in adults aged ≥59 years recruited from geriatric and memory clinics and facilities for seniors, the SAGE had a PPV of 64%, a NPV of 95%, a sensitivity of 79%, and a specificity of 95% with regard to diagnosing cognitive impairment [12]. In a memory clinic population, the TYM had a specificity of 95%, a sensitivity of 81%, a PPV of 64%, and a NPV of 98% at a cutoff score of 39 points for Alzheimer's disease. In our view, a new cognitive test should have a PPV comparable with that of the most commonly used instrument, the MMSE, which has a PPV of 53.6% for the diagnosis of dementia in primary care [29]. Therefore, for our sample size calculation, we set the lower margin for the estimated PPV at 53% (ie, 11% below the previously established PPV of 64%). With this margin and an alpha of 5% and one-sided testing (we are only interested in the lowest 5% of cognitive scores), 52 participants with a positive test result (0.11= 1.65*√(0.64*(1-0.64)/n)) are needed to have reliable, interpretable results. To achieve this number of test positive participants, given an assumed prevalence of 8% and a sensitivity of 79%, 513 participants are required. Given the test features of the TYM, this sample size should also be sufficient to determine the accuracy of the TYM. As participants will be referred to the memory clinic based on the results of all 3 tests (TYM, SAGE, and evaluation by the GP), and the results of the tests will probably not completely overlap, the group "suspected of cognitive impairment" will be larger than the group that will be tested positive on the SAGE alone. We estimate that the former group will be 50% larger than the SAGE-positive group (ie, 78 people are estimated to be in the group “suspected of cognitive impairment”). All these 78 participants will be invited to attend the memory clinic in order to establish the true and false positive rates of each of the tests. In addition, a sample (14.9%, 65/435) of the participants in which all 3 tests are negative (the screen-negatives) will be invited to the memory clinic to establish the true and false negative rates of each test. Hence, 143 participants in total will be evaluated at the memory clinic (Figure 1).

Because of uncertainty on the actual prevalence of undiagnosed cognitive impairment in our cohort, an interim analysis is planned after the inclusion of 80 participants. During this interim analysis, only the proportion of participants classified as "suspected of cognitive impairment" will be checked without unblinding the test scores or the findings at the memory clinic. If the proportion deviates significantly from our assumptions we will adjust the sample size of the study population accordingly.

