### Statistical Analysis

The diagnosis of cognitive impairment (MCI or dementia) at the memory clinic will be used as the reference standard. To address the first two objectives, participants will be classified as true positive, false positive, false negative, or true negative separately for the evaluation by the GP, TYM, and SAGE.

Not all of the patients in our study will receive the reference standard, which could lead to partial verification bias [25]. However, if only patients with the reference standard were included in the analysis (complete case analyses), the results would be biased because the selection of the patients with the reference standard will not be at random [25]. A reliable method to reduce this bias is to impute the reference standard [25]. A cognitive impairment diagnosis (yes or no) in the memory clinic will, therefore, be imputed for patients who did not attend the memory clinic. Imputed databases (N=10) will be generated with the predictors TYM, SAGE, MMSE, GP evaluation, as well as age, gender, educational level, living situation, and score on the domain mobility of the EQ-5D. The latter two are chosen because they can influence why some patients did not attend the memory clinic. With these imputed numbers, the sensitivity, specificity, positive predictive value (PPV), and negative predictive value (NPV) will be calculated.

The extent to which the cognitive tests and the evaluation by the GP discriminate between participants with and without cognitive impairment will be determined by the area under the receiver operating characteristic (ROC) curve. Next, the optimal cutoff values of the tests for this population will be determined according to the best combination of corresponding sensitivity and specificity assessed with the Youden index. The Youden index measures the effectiveness of a diagnostic marker and enables the selection of an optimal cutoff point [26]. By means of the ROC curve and the best combination of diagnostic values, the optimal instrument will be selected.

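### The sample size section counts all 143 invited participants as evaluated, although the analysis section expects some not to attend, so the stated PPV precision holds only at full attendance

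*Protocol article*

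**What the plan says.** In the Sample Size Calculation, the PPV target is set with "an alpha of 5% and one-sided testing", an expected PPV of 64% and a lower margin of 53%. From this, "52 participants with a positive test result (0.11= 1.65*√(0.64*(1-0.64)/n)) are needed". The any-test-positive group is taken to be 50% larger than the SAGE-positive group, giving 78, and "All these 78 participants will be invited to attend the memory clinic". In addition, "a sample (14.9%, 65/435) of the participants in which all 3 tests are negative" is to be invited. The section then concludes that "143 participants in total will be evaluated at the memory clinic".

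The Statistical Analysis section imputes the memory clinic diagnosis for everyone who did not attend. Living situation and EQ-5D mobility are among the predictors, and the reason given is: "The latter two are chosen because they can influence why some patients did not attend the memory clinic".

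The section on selection for the memory clinic visit makes invitation depend only on the three test criteria and, for screen-negatives, on a random draw. The interim check after 80 participants looks only at the proportion suspected of cognitive impairment.

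**The concern.** Living situation and mobility play no part in who is invited. They can bear on non-attendance only among people who were invited and did not come. The analysis section therefore foresees missing reference diagnoses among invitees, while the sample size section allows for none.

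Two design figures depend on this. The first is the PPV margin, because its formula is a binomial standard error in which each of the *n* positives has an observed diagnosis (the formula implies this; the text does not say so). The second is the screen-negative sample. Each of the 65 invited stands for 435/65 = 6.7 people, so every loss there weakens the estimates of sensitivity and NPV. The interim check would not reveal a shortfall, because it does not look at attendance.

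**Working it through.** **Inputs from the Sample Size Calculation:** expected PPV 0.64; margin 0.11; multiplier 1.65; 52 test positives; 78 suspected; 65 of 435 screen-negatives; 513 participants. **Assumed input:** the attendance *a* among invitees. The protocol article gives no figure, so 90%, 80% and 70% are used.

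**Step 1: reproduce the plan's figures.**
- Positives needed: 1.65² × 0.64 × 0.36 / 0.11² = 51.84, rounded up to 52.
- Suspected group: 52 × 1.5 = 78. Remainder: 513 − 78 = 435. Sampling fraction: 65/435 = 14.9%. Total: 78 + 65 = 143.
- Cohort: 52 × 0.64 / (0.79 × 0.08) = 526.6, close to the stated 513 (with the TYM sensitivity of 81% it is 513.6). The steps below take the plan's 52 positives as given, so they do not depend on this difference.

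**Step 2: slack at full attendance.**
- 52 verified: 1.65 × √(0.64 × 0.36 / 52) = 0.1098, lower limit 53.02%.
- 51 verified: 1.65 × √(0.64 × 0.36 / 51) = 0.1109, lower limit 52.9%.

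A single unverified positive takes the nominal limit below 53%.

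**Step 3: PPV at reduced attendance.** Verified positives = 52*a*; half-width = 1.65 × √(0.64 × 0.36 / (52*a*)). This treats non-attenders as contributing nothing, so it is a worst case.

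| Attendance (assumed) | Verified positives | Half-width (points) | Lower limit | Evaluated, of 143 |
|---|---|---|---|---|
| 100% | 52 | 11.0 | 53.0% | 143 |
| 90% | 46.8 (about 47) | 11.6 | 52.4% | 129 |
| 80% | 41.6 (about 42) | 12.3 | 51.7% | 114 |
| 70% | 36.4 (about 36) | 13.1 | 50.9% | 100 |

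**Step 4: screen-negatives.** With 65 invited, 65*a* attend: 58.5, 52 and 45.5 at 90%, 80% and 70%. Each attender then stands for 435/58.5 = 7.4, 435/52 = 8.4 or 435/45.5 = 9.6 people. To have 65 attend, 65/*a* must be invited: about 72 at 90% and about 93 at 70%, which is 93 − 65 = 28 more than planned.

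**The case against.** Several points on the other side are sound.

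- **The arithmetic is right on its own inputs.** 52, 78, 435, 65/435 and 143 all check, and the operational rule (who is invited) is clear. What is missing is a planning assumption, and one word hides its absence. A reader might infer a calculation error; the protocol article does not support that.
- **Falling below 53% is close to automatic.** The number 52 was solved to land on 53%, so any loss crosses it. A reader might infer that the study would then fail. But 53% is a margin chosen for interpretable results, comparable with the PPV cited for the MMSE, and no success rule is attached to it.
- **Imputation is worth something.** Non-attenders' diagnoses are imputed from TYM, SAGE, MMSE, the GP evaluation and demographic variables. If these predict well, part of the lost information returns, so the table in the working overstates the loss. It does not remove the point: an imputed diagnosis does not equal an observed one, and the formula with n = 52 has no between-imputation variance.
- **Other inputs are uncertain too.** The 8% prevalence and the 50% enlargement are assumptions, and the cohort may be resized after 80 participants. That check does not monitor attendance, so it offers no protection here.
- **The 65 are not the only source for sensitivity and NPV.** By the plan's own estimate, 78 − 52 = 26 suspected participants are SAGE-negative and are also invited for verification.

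**Conclusion.** The point holds as an inconsistency between two sections: non-attendance is expected in the analysis and ignored in the sample size. The stated 11-point margin and 53% lower limit apply only if every test positive attends.

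The size is moderate. Under assumed attendance of 90% to 70%, the lower limit falls by about 0.6 to 2.1 points in a calculation that gives imputation no credit; the true loss is probably smaller. The attendance range is an assumption, since the protocol article gives no rate. It would be too strong to say that the design cannot estimate the PPV usefully, or that the cohort has to grow. What is not supported is the precision as stated.

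**What to change.** 1. In the Sample Size Calculation, change 'evaluated' to 'invited' for the 143. State an expected attendance, and restate the expected number verified and the PPV precision at that attendance. At 80%, for example, that is about 114 evaluated, 42 verified positives and a half-width of 12.3 points before any gain from imputation. The cohort need not be enlarged. Holding 52 verified positives instead would take 513/0.9 = 570 to 513/0.7 = 733 participants, a much larger cost.
2. Separately, for sensitivity and NPV, draw the screen-negative sample from a randomly ordered list and continue down it until 65 have attended. Keep non-attenders in the imputation, because replacing them restores the count but does not remove selective attendance.

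The second step does nothing for PPV precision: every test positive is already invited and none can be replaced.

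The cost is a less favourable stated precision and up to about 28 more invitations. On the plan's own estimates, clinic visits stay at no more than 78 + 65 = 143.

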#### Part 2: Selection Criteria for Memory Clinic Visit

After the home visit, an independent physician, not involved in the home visit or in the memory clinic, will determine whether the participant will be selected for a visit to the memory clinic of the University Medical Centre Utrecht. To minimize the influence of the increasing experience of the research physician because of the growing number of home visits during the study period, the research physician who visited the participant at home will not be informed about the results of the memory clinic. The following 3 criteria will be used to decide whether a participant will be invited to the memory clinic (1) a classification of “suspected of cognitive impairment” by the research physician, (2) a score of ≤39 on the TYM, and (3) a score of ≤14 on the SAGE. When a participant scores positive on one of these criteria, the participant will be invited to the memory clinic. In addition, a random sample of 15% (65/435) of participants with negative scores on all 3 criteria will be invited to the memory clinic (see sample calculation below and Figure 1).

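### The interim check resizes the study on the proportion suspected of cognitive impairment, but N was derived from positives on a single test, and the assumed ratio of 1.5 that links them is not checked

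*Protocol article*

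**What the plan says.** All of this is in the Protocol article.

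- **Sample Size Calculation, target.** The requirement is for one test: "52 participants with a positive test result (0.11= 1.65*√(0.64*(1-0.64)/n)) are needed". The total follows from SAGE inputs: "given an assumed prevalence of 8% and a sensitivity of 79%, 513 participants are required". The same total is said to suffice for the TYM.
- **Sample Size Calculation, referral group.** People positive on any of TYM, SAGE or GP evaluation are expected to outnumber the SAGE positives: "We estimate that the former group will be 50% larger than the SAGE-positive group". That gives 78 people.
- **Part 2: Selection Criteria for Memory Clinic Visit.** The referral rule is any one of three criteria: "When a participant scores positive on one of these criteria, the participant will be invited to the memory clinic". An independent physician, involved in neither the home visit nor the memory clinic, applies it.
- **Sample Size Calculation, interim.** After 80 inclusions, only the proportion classified as suspected of cognitive impairment is examined, with test scores and clinic findings kept blinded. Then: "If the proportion deviates significantly from our assumptions we will adjust the sample size of the study population accordingly". The reason given is uncertainty about prevalence.

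The label is used in two ways. The home-visit section and the first criterion of Part 2 apply it to the research physician's classification alone. The Abstract and the Sample Size Calculation apply it to the any-of-three group.

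**The concern.** The quantity that triggers a change of N is not the quantity from which N was derived. The any-of-three proportion is only an upper limit on the proportion positive on each test. It gives the right N only if it is really 1.5 times the SAGE-positive proportion, and nothing in the interim tests that.

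The error can go either way. If the physician's evaluation supplies most of the suspects, the check can look on target while SAGE or TYM positives fall short. If the physician flags many extra people and SAGE runs as planned, the check can prompt a reduction that removes precision the study would otherwise have had.

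A large physician share is plausible from the protocol itself. The TYM and SAGE cut-offs are described as suggestive of dementia, whereas the physician classifies by criteria for both MCI and dementia.

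**Working it through.** **Inputs from the Sample Size Calculation:** expected PPV 0.64, margin 0.11, z = 1.65, prevalence 8%, SAGE sensitivity 79%, N = 513, any-of-three group 1.5 times the SAGE-positive group, interim at 80.

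**1. The plan's own figures**

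- Positives needed: 1.65² × 0.64 × 0.36 / 0.11² = 51.84, so 52. The TYM is quoted with the same PPV of 64%, so the same 52 would apply to it.
- Total: 52 × 0.64 / (0.08 × 0.79) = 526.6, within 3% of 513. The stated figure matches 52 × 0.79 / 0.08 = 513.5 more closely. That difference is small and is not the point here.
- Any-of-three group: 1.5 × 52 = 78; 513 − 78 = 435; 65/435 = 14.9%; 78 + 65 = 143.
- As proportions: SAGE 52/513 = 10.1%, or 8.1 of 80; any-of-three 78/513 = 15.2%, or 12.2 of 80.

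**2. Any-of-three proportion exactly on plan, ratio varied**

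SAGE positives = 78 / ratio. Margin = 1.65 × √(0.64 × 0.36 / positives). N needed for 52 positives = 513 × ratio / 1.5. Ratios other than 1.5 are assumptions, and PPV is held at 64%.

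| Ratio | SAGE positives at 513 | Expected in 80 | Margin | Lower bound | N for 52 positives |
|---|---|---|---|---|---|
| 1.5 (plan) | 52 | 8.1 | 11.0 points | 53.0% | 513 |
| 2 | 39 | 6.1 | 12.7 | 51.3% | 684 |
| 3 | 26 | 4.1 | 15.5 | 48.5% | 1,026 |
| 4 | 19.5 | 3.0 | 17.9 | 46.1% | 1,368 |

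Every row shows the interim the same 12.2 of 80. The protocol gives no threshold for a significant deviation. If it is taken as an exact two-sided 5% test against 15.2%, it signals at ≤5 or ≥20 of 80. With the any-of-three proportion on plan it then signals about 2.8% of the time, whatever the SAGE count.

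**3. The opposite error**

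Assume SAGE at the planned 10.1% and the any-of-three proportion at 25%, so 20 of 80 expected, which is on the upper signal limit. If N is scaled in proportion (also an assumption, since the rule is not stated): 78 / 0.25 = 312. SAGE positives = 312 × 52/513 = 31.6. Margin = 1.65 × √(0.2304 / 31.6) = 14.1 points, against 11 had N stayed at 513.

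**4. How well a SAGE count would do at 80**

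Against 10.1%, the lower limit of an exact two-sided 5% test is ≤2 of 80. If the true SAGE-positive rate is 5%, P(X ≤ 2) = 23%. An observed 4 of 80 has an exact 95% confidence interval of 1.4% to 12.3%.

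**The case against.** **The check is about prevalence, not the PPV margin.** That is its stated motive. Its stated action, however, is to change N, and N was defined by single-test positives. The mismatch remains.

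**Too few positives need not breach the 53% floor.** This is correct, and it limits the claim. A reader might infer that a shortfall of test positives by itself takes the lower bound below 53%. The documents do not support that, because a stricter test can have both fewer positives and a higher PPV. For example, at 8% prevalence, sensitivity 45% and specificity 98.5% (assumed) give 0.036 / (0.036 + 0.0138) = 72% PPV and about 25.5 positives at 513. The margin is 1.65 × √(0.723 × 0.277 / 25.5) = 14.6 points and the lower limit about 58%. The bounds in the table hold only at the plan's own PPV of 64%. What always follows from fewer positives at a given PPV is a wider margin.

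**The label may mean the physician's classification alone.** Two sections use it that way. The check would then not register SAGE or TYM positives and would have no stated reference value, so this reading does not rescue the rule. The any-of-three reading fits better because only that group has an assumed size.

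**A count of about 8 in 80 is too noisy.** This largely stands: a halved rate would be detected less than a quarter of the time. It argues for an interval and a repeat count, not for relying on a proportion that need not reflect the target.

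**Cut-offs will be re-selected.** The Statistical Analysis section chooses cut-offs by the Youden index, so counts at the published cut-offs do not settle final precision. That is true, but the 52 was derived from performance reported for the published tests, and the referral rule uses those cut-offs.

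**Blinding.** The independent physician already applies both cut-offs. Aggregate counts reveal no individual score and no clinic finding.

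**Conclusion.** The point holds in a limited form. The interim rule changes N on a quantity that determines the required number only through an unchecked ratio of 1.5. With the any-of-three proportion on plan and PPV at 64%, a ratio of 2 means 39 SAGE positives and a lower bound of 51.3%; a ratio of 3 means 26 and 48.5%. In the other direction, a 25% any-of-three proportion with SAGE on plan could cut N to 312 and widen the margin from 11 to about 14 points.

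The ratios, the 25%, the proportional scaling and the 5% test are assumptions, and the documents do not say that any of these cases is likely. A reader might go further and conclude that the study will miss its PPV criterion, or that the check has no use. Neither follows: the ratio of 1.5 may prove right, and the any-of-three proportion does inform memory clinic load. This is an inexpensive improvement of optional to modest priority.

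**What to change.** In the interim paragraph of the Sample Size Calculation:

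1. State that *suspected* means positive on any of the three criteria.
2. Have the independent physician who applies the referral criteria also report the aggregate numbers with SAGE ≤14 and with TYM ≤39, without individual scores or clinic findings.
3. Base any change of N on the projected SAGE and TYM positives against the target of 52. Use the any-of-three proportion only to plan memory clinic load.
4. Report each count with its confidence interval, repeat it at a later enrolment point, and do not reduce N on the any-of-three proportion alone.

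The cost is a few sentences and two counts that the independent physician can already produce; blinding is unchanged. The drawback is imprecision at 80 participants, which is why the repeat count is needed.

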### Regulation Statement

This study will be conducted according to the principles of the declaration of Helsinki and in accordance with the Dutch law on Medical Research Involving Human Subjects Act (WMO).

### Ethics Committee Approval

The cognitive impairment in diabetes (Cog-ID) study was approved by the medical ethics committee of the University Medical Centre Utrecht, the Netherlands. Written informed consent will be obtained from all participants.

## Results

Funding was obtained through the EFSD/Lilly Mental Health and Diabetes Program in 2012. Participant enrolment started in August, 2012. All study-related activities will be completed in September, 2016. The first results are expected to be published in 2015.

## Discussion

This cognitive impairment in diabetes (Cog-ID) study will provide a stepped diagnostic procedure to identify patients with type 2 diabetes and undiagnosed cognitive impairment, which can be readily implemented in daily practice. This is essential to improve the care for this vulnerable patient group. We will have information on the diagnostic accuracy of two new cognitive tests, the TYM and the SAGE, and whether these tests can be used in a diagnostic procedure (ie, combining a cognitive test with history taking by a GP) to detect cognitive impairment in primary care. In addition, we will collect observational data on the impact of such diagnostic procedures on several aspects of patients’ lives (health status, depressive symptoms, complications, and diabetes treatment) after 6 and 24 months. Physicians often assume that informing the patient about a diagnosis of cognitive impairment will negatively influence their health status, quality of life, and depressive symptoms [30]. However, one could also argue that undiagnosed cognitive impairment might cause a reduced quality of life and depressive symptoms, because it is likely to impact patients. If these aspects of patients' lives are affected by undiagnosed cognitive impairment, and could be ameliorated by informing the patient, then the tailoring and possibly the adjustment of treatment and/or organizing support could be another argument as to the importance of detecting cognitive impairment at an early stage.

A potential bias in diagnostic studies in which not all patients receive the reference standard is partial verification bias [25]. However, we will try to reduce this verification bias by imputing the reference standard in participants that do not visit the memory clinic. This method has been shown to give reliable estimates of missing reference data [25].

With the information from this study, we can advise GPs on how to assess cognitive functioning in their patients so they can adjust diabetes treatment to the preserved capacities of their patients, as advocated by the American Diabetes Association, and consequently might prevent treatment-related complications. In addition, the results will form a base for future discussions on whether the early recognition of cognitive impairment in patients with type 2 diabetes with a case-finding strategy is desirable.

